### Eligibility criteria

Patients aged ≥ 18 years, undergoing CABG, valve surgery, or isolated aortic surgery will be included in the study. To allow implementation of a prehabilitative strategy, surgeries must be scheduled at least 14 days after enrollment (Table 1).

**Table 1 Tab1:** Study inclusion and exclusion criteria

Inclusion criteria	
1. Aged ≥ 18 years	
2. Undergoing any of the following types of cardiac surgery: CABG with or without valve surgery (aortic and/or mitral); isolated valve surgery; isolated aortic surgery	
3. Surgery scheduled for at least 14 days after enrollment	
Exclusion criteria	
1. Urgent and/or emergent surgery	
2. Non-English speaking	
3. Pre-existing history of psychiatric illness as documented in the medical record or divulged in history taking in pre-enrollment patient interview, such as anxiety, depression, or bipolar disorder	
4. History of cerebrovascular accident or recent history (< 3 months) of seizures	
5. History of dementia, Parkinson’s disease, Alzheimer’s disease, or other forms of cognitive decline	
6. Current use of cognition-enhancing drugs	
7. Current management for chronic pain	
8. Currently enrolled in another interventional study that could impact the primary outcome, as determined by the PI	
9. Educational attainment below high school level or equivalent	
10. Significant visual impairment	
Preoperative dropout criteria	
1. Cognitive impairment as defined by MoCA score < 10	
2. DASS-21 depression score > 10	

Patients undergoing urgent or emergent procedures or those undergoing only minimally invasive cardiac procedures will be excluded. Non-English-speaking patients and those with significant visual impairment will also be excluded, as these factors preclude performing neurocognitive assessments. Patients who do not have high-school level or the equivalent educational attainment, patients with moderate to severe cognitive impairment as defined by baseline Montreal Cognitive Assessment (MoCA) < 10 and those on cognition-enhancing drugs will be excluded. Patients with a history of cognitive impairment and psychiatric illnesses will be excluded. Patients who are actively taking pain medications will be excluded. Patients who are currently enrolled in another interventional study that could potentially impact the primary outcome will also be excluded from the study.

### Recruitment and randomization

Individuals will be identified from perioperative surgical consult lists and cardiac surgery clinic visit schedules. If a candidate is eligible for enrollment, he or she will be approached by a member of the research team to discuss the study in detail. Written informed consent will be obtained before initiation of any study procedures.

After obtaining consent, enrolled participants will be randomly assigned to one of three groups using block randomization in a 1:1:1 allocation. REDCap will be utilized to implement the randomization schema while maintaining the blind. REDCap is a secure software designed for rapid data capture tools using metadata table referenced by presentation-level operational modules [24]. Patients will be randomized to one of the following groups:Group 1: Patients are asked to meditate twice daily, starting from least two weeks before surgery, up until four weeks after surgery;Group 2: Patients are asked to meditate twice daily from the day after surgery until four weeks after surgery;Group 3: Patients in the control group will undergo surgery and subsequent hospital stay according to the current standard of care, which does not include meditation.

Patients who are actively meditating previously and are willing to participate in the study will be asked to refrain from meditating during the study period if they are randomized to the control group. They will be required to follow the IK meditation schedule during the period of study participation if they are randomized to one of the intervention groups.

The inclusion of a control group will allow for quantification of the natural history of surgery and postoperative complications. Further, we are utilizing two interventional groups to assess whether a prehabilitative strategy results in differences as compared to a mitigation strategy. Two intervention groups will also help us determine the optimal duration of intervention and the possible impact of duration on compliance and other secondary outcomes.

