**Methods:**

This is a prospective, randomized controlled feasibility trial. A total of 40 adult patients undergoing cardiac surgery will be randomized to one of three study groups. Participants randomized to either of the two intervention groups will receive meditative intervention: (1) commencing two weeks before surgery; or (2) commencing only from the day after surgery. Meditative intervention will last for four weeks after the surgery in these groups. Participants in the third control group will receive the current standard of care with no meditative intervention. All participants will undergo assessments using neurocognitive, sleep, depression, anxiety, and pain questionnaires at various time points in the perioperative period. Blood samples will be collected at baseline, preoperatively, and postoperatively to assess for inflammatory biomarkers. The primary aim of this trial is to assess the feasibility of implementing a perioperative meditative intervention program. Other objectives include studying the effect of meditation on postoperative pain, sleep, psychological wellbeing, cognitive function, and delirium. These will be used to calculate effect size to design future studies.

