**Fig. 1 Fig1:**
[figure not shown]
Meditation instructions. Participants in either mediation group are provided with the instructions depicted here. In short, this includes preparation and three stages in which the participant mindfully inhales and exhales slowly for 7 min, produces the sound “Ahh” seven times, and finishes with 5 min of being quiet

At the time of enrollment, individuals randomized to Groups 1 and 2 are introduced to the meditation by a trained unblinded study team member. The participant is walked through the instructions and is then allowed to practice the technique with the instructor’s guidance. Participants who are randomized to meditate only after surgery will be asked to complete the practice once to ensure they are comfortable with the instructions and to otherwise refrain from meditating until after surgery. Unblinded study team members will not conduct any other subsequent subjective study assessments to reduce any bias associated with interpreting results.

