### Neurocognitive and psychological assessments

A trained research team member who remains blinded to treatment allocation will perform baseline cognitive, delirium, anxiety, and depression assessments. Cognitive function will be assessed using the Montreal Cognitive Assessment (MoCA), supplemented with days of the week (DOW) and months of the year (MOY) for additional attention testing. The Delirium Symptom Interview (DSI) will be used to capture delirium. The Depression, Anxiety, and Stress scale (DASS-21) will be used to assess the baseline psychological state. Using data from the cognitive testing and DSI, the researcher will complete the Confusion Assessment Method (CAM), which includes an assessment of delirium using the CAM diagnostic algorithm. If this baseline assessment shows a DASS-21 depression score > 10 or MoCA score < 10, the individual will be excluded from the study.

To assess the changes over time, or the possible effect of perioperative meditation, a telephonic MoCA (t-MOCA) will be administered preoperatively within 24 h before surgery. These assessments will take place before initiation of any sedatives or other medications that may affect the patient’s performance or ability to complete the assessment.

On each postoperative day during the hospital stay, a blinded research team member will administer a standard cognitive assessment, including DOW, MOY, CAM, and the DSI. If an individual is intubated postoperatively, a CAM-ICU will be performed instead of a CAM assessment. If daily assessments have plateaued for three consecutive days and the patient remains CAM-negative each day, assessments will then be completed every other day if the individual remains CAM-negative, until the date of discharge. On the day of discharge, the MoCA, DOW, MOY, CAM, DSI, and the DASS-21 will be completed.

A follow-up assessment will be administered at one month (± seven days) after the date of surgery. These will be completed by a blinded research team member via telephone and will include a T-MoCA, DOW, MOY, CAM, DSI, and DASS-21. Medications that were taken 6 h before the assessments, as reported per the individual, will be documented at all time points.

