### Statistical analysis

In this feasibility study, a convenience sample of 30 participants (10 per group) will be enrolled to assess feasibility. While we expect it to be very rare, it is possible that some individuals may be determined ineligible after signing consent (because of their baseline MoCA or DASS-21 depression scores). Therefore, we plan to enroll enough patients to obtain data from 30 randomized participants. We estimate that approximately 40 patients may be enrolled to account for dropouts, loss of follow-up, and to achieve this sample size of 30. No a priori power calculation was performed.

Since the primary outcome of the study assesses the overall feasibility of conducting the trial, our descriptive study will record the proportion of patients eligible who meet inclusion without exclusion criteria and decide to participate. The statistics for overall protocol adherence to the intervention will be recorded by reporting the total number of sessions completed out of that required per protocol. We will also assess the total number of questionnaires completed out of the total required.

Descriptive statistics of data will be performed. Categorical data will be reported as proportions and assessed with the use of a chi-square or Fisher’s exact test. Continuous data will be reported as means ± standard deviations or median (quartile 1 and quartile 3) depending on distribution and assessed using analysis of variance (ANOVA). We estimate that with a small sample size it may not be acceptable to assume normality and may be appropriate to use a non-parametric equivalent such as Kruskal–Wallis test when appropriate. A trajectory analysis will be performed to assess changes in the presence of delirium or changes in cognitive function over time. Since the secondary outcomes are exploratory in nature, all tests will be two-sided, with *p* values < 0.05 considered statistically significant. Data will be analyzed using SAS 9.4 (SAS Institute Inc., Cary, NC, USA) or later. Our primary analysis will be conducted using the intention-to-treat principle. All trial reporting will adhere to the Standard Protocol Items: Recommendations for Interventional Trials (SPIRIT; Additional file 1: Table S1).

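### The number randomised is given as both 40 and 30, a target of 30 with data does not fit intention to treat, and the order of allocation and baseline eligibility testing is not fixed

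*Protocol article*

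**What the plan says.** **Numbers.** The abstract (Methods) states: "A total of 40 adult patients undergoing cardiac surgery will be randomized to one of three study groups". The Statistical analysis section opens with a convenience sample of 30 enrolled, 10 per group. It then says "we plan to enroll enough patients to obtain data from 30 randomized participants" and estimates that about 40 may be enrolled, to cover dropouts and loss to follow-up. Limitations repeats 40 enrolled to reach 30. No attrition rate and no power calculation are given.

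**Analysis principle.** The same Statistical analysis section states: "Our primary analysis will be conducted using the intention-to-treat principle".

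**Order of events.** Recruitment and randomization: "After obtaining consent, enrolled participants will be randomly assigned to one of three groups using block randomization in a 1:1:1 allocation". Study intervention: "At the time of enrollment, individuals randomized to Groups 1 and 2 are introduced to the meditation by a trained unblinded study team member". Neurocognitive and psychological assessments: "A trained research team member who remains blinded to treatment allocation will perform baseline cognitive, delirium, anxiety, and depression assessments".

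**Removal on baseline scores.** That last section goes on to say that with a baseline DASS-21 depression score above 10 or a MoCA below 10, "the individual will be excluded from the study". Table 1 sets the same two thresholds apart from the exclusion criteria, under a preoperative dropout heading. The text below Table 1 lists the MoCA threshold among the exclusions.

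**The concern.** The primary outcome is adherence: sessions completed divided by sessions required, taken from the diaries of the two meditation groups. Future direction says that reasonable compliance will denote feasibility and support a larger study. Participants who withdraw or are lost are likely to be the least adherent. Whether the trial is described by those randomised or by those who supplied data therefore bears directly on its main result, and the article points both ways.

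The second issue is timing. If the MoCA and DASS-21 are scored after allocation, people can be removed from a randomised group on scores obtained once they know their arm, and in Groups 1 and 2 possibly after a first guided practice. Removal could then differ by arm. The self-reported baseline could also be influenced by knowledge of the arm, which would affect the effect sizes meant to inform the next trial. The article does not rule this order out.

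**Working it through.** **1. The plan's own figure.** There is no effect size, power or attrition rate, so 40 cannot be derived forwards. Solving backwards with N enrolled = N target / (1 − loss):

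- 40 = 30 / (1 − d), so d = 1 − 30/40 = 0.25.
- Smaller losses need fewer people, rounding up: 30/0.95 gives 32, 30/0.90 gives 34, 30/0.85 gives 36, 30/0.80 gives 38.

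The step from 30 to 40 therefore implies a loss of up to 25%.

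**2. Can the statements on N be reconciled?**

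| Reading | Randomised | What it contradicts |
|---|---|---|
| A. 40 consent, baseline screen, 30 randomised | 30 (10 per arm) | The abstract's 40 randomised. It also leaves no allowance for losses after randomisation, although the statistics section names loss to follow-up as a reason for the extra patients. |
| B. 40 randomised, 30 supply data | 40 (40/3 = 13.3, so 13, 13 and 14) | The opening statement of 30 enrolled, 10 per group. Under intention to treat, 40 are analysed, and 30 is an available-data subset that omits 10 of 40. |

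An intermediate reading, with between 30 and 40 randomised, contradicts the abstract as well. The statistics section expects ineligibility on baseline scores to be very rare, so most of the 10 extra patients must be there for dropouts and losses, which arise mainly after randomisation. That favours reading B, but the text does not settle it.

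**3. Order of allocation and baseline scoring.**

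- *For allocation first:* randomisation is placed after consent with no completed baseline screen as a condition; Groups 1 and 2 are already randomised when taught at enrolment; the baseline assessor is described as blinded to allocation; Table 1 uses a dropout label.
- *For scoring first:* the text under Table 1 (MoCA) and the assessment section (both scores) treat the thresholds as exclusions; the statistics section speaks of people found ineligible after consent and then counts randomised participants.

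No sentence places one before the other.

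**4. Size for the primary outcome (illustration).** Let a be adherence among those kept and d the share of the meditation groups omitted. Assume that losses are proportional across arms and that each person lost contributes zero sessions. Adherence over all randomised to meditation is then a × (1 − d):

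| a | d = 5% | d = 15% | d = 25% |
|---|---|---|---|
| 70% | 66.5% | 59.5% | 52.5% |
| 80% | 76% | 68% | 60% |
| 90% | 85.5% | 76.5% | 67.5% |

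If those lost had completed a share f of their sessions, the figure is a(1 − d) + f·d, which lies closer to a. The table therefore shows the largest effect at each d.

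**The case against.** Several stronger readings are tempting, and the article does not support them.

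- *Participants are randomised straight after consent and then excluded.* This is the more natural reading, but it is not stated. One enrolment visit could run consent, baseline tests, allocation and then teaching. Blinding of the assessor describes a role and does not date the allocation. The SPIRIT schedule (Fig. 2) is not shown and may settle the order.
- *Dropouts are replaced.* The article describes over-enrolment for expected attrition, which is ordinary practice. It contains no rule for refilling a place.
- *Adherence will be analysed only in the 30 with data, so the intention-to-treat set is not what was randomised.* No passage restricts the analysis in this way. The adherence definition uses sessions required by protocol and is not limited to completers, and intention to treat is stated for the primary analysis. A detailed set definition may sit in an analysis plan that is not shown.
- *Adherence would be inflated by a third (80% against 60%).* This needs all 10 extra patients lost after randomisation, losses proportional across arms, and no sessions from any of them. Only Groups 1 and 2 keep diaries, so some of the 10 would probably be controls. Someone lost at one month may have meditated for weeks.

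It is also fair that the sample is one of convenience, so no power figure changes, and that the secondary outcomes are hypothesis generating. What remains is a contradiction between printed statements on N, a target worded in terms of available data beside an intention-to-treat claim, and a sequence left open by conflicting labels. An unseen document does not remove the contradictions in this one.

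**Conclusion.** The point holds in three parts of unequal strength. The conflict on the number randomised is firm: 40 in the abstract cannot stand with 30 enrolled, about 40 enrolled and data from 30 randomised. The mismatch between a target of 30 with data and intention to treat is also firm as wording, whichever way the timing is resolved; that the analysis itself would be completer-only is not shown. On timing, removal on baseline scores after allocation is possible and is the more natural reading, but the finding is that the order is badly fixed, not that it is wrong.

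For an adherence of 80% among those kept, the consequence ranges from 4 percentage points at 5% loss to 20 at 25% loss, under proportional losses and zero sessions for those lost. The 25% is an upper bound implied by 30 of 40, not a rate that the article states. Because adherence decides feasibility, this deserves correction while recruitment is still open.

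**What to change.** 1. State that the baseline MoCA and DASS-21 are completed and scored before REDCap releases the allocation. Reconcile Table 1 with the text under it and with the assessment section on whether the two thresholds are exclusions or dropouts. If anyone is removed on them after allocation, keep that person in the intention-to-treat set.
2. Give one number each for consented, randomised and analysed, identical in the abstract, the Statistical analysis section and Limitations.
3. Define the sample by the number randomised, not by the number with data.
4. Report adherence in everyone randomised to Groups 1 and 2, counting sessions not done after withdrawal as not completed. Show the available-data figure as a sensitivity analysis.

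The cost is wording, the order of one visit and a possibly less favourable adherence figure. No patients are added.

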### Study intervention

IK meditation is a type of meditation that focuses on thought and mindful breathing and takes approximately 12 min to complete. This regimen was chosen because it excels in simplicity and is a great way to introduce meditation to beginners. Further, it does not incorporate any spiritual or religious focus. “Kriya” means an internal action, which is focusing on a specific thought in this case [25].

In brief, the participant first begins preparing for the IK practice by sitting in a cross-legged posture or sitting in a chair, spine comfortably erect, hands on their thighs, palms facing up, face slightly upturned, eyes closed, all while keeping a mild focus between the eyebrows. He or she can start meditating by slowly inhaling and exhaling while mentally focusing on the thoughts “I am not the body” during inhalation and “I am not even the mind” during exhalation. This is continued for 7 min. This is followed by uttering a long “Ahh” sound seven times. The individuals are instructed to exhale through the sound and utter the sound loud enough to feel a vibration around the mid-abdomen. The third step in the process is to sit still for 5 min with the eyes closed, as detailed in Fig. 1. This practice is to be repeated twice daily.

**Fig. 1 Fig1:**
[figure not shown]
Meditation instructions. Participants in either mediation group are provided with the instructions depicted here. In short, this includes preparation and three stages in which the participant mindfully inhales and exhales slowly for 7 min, produces the sound “Ahh” seven times, and finishes with 5 min of being quiet

At the time of enrollment, individuals randomized to Groups 1 and 2 are introduced to the meditation by a trained unblinded study team member. The participant is walked through the instructions and is then allowed to practice the technique with the instructor’s guidance. Participants who are randomized to meditate only after surgery will be asked to complete the practice once to ensure they are comfortable with the instructions and to otherwise refrain from meditating until after surgery. Unblinded study team members will not conduct any other subsequent subjective study assessments to reduce any bias associated with interpreting results.

### Study outcomes

The primary outcome of the study is to assess the feasibility of implementing a meditation routine in the perioperative period. This will be evaluated using the adherence data from patients’ meditation diary. Secondary exploratory outcomes include effects of the intervention on pain, sleep, psychological wellbeing, cognitive function, and delirium. A number of tools, including pain scores, questionnaires for cognition and delirium assessment, depression and anxiety questionnaire, sleep questionnaires, total opioid consumption and supplemental analgesic requirements in the first 48 h postoperatively, Intensive Care Unit (ICU) stay, and hospital length of stay, will be used to measure the secondary outcomes. In addition, we will also evaluate inflammatory biomarkers measured in plasma. All secondary outcomes will be considered hypothesis generating and interpreted as such (Fig. 2).

**Fig. 2 Fig2:**
[figure not shown]
SPIRIT figure. The schedule of enrolment, interventions, and assessments in the study

### Meditation adherence

To assess study feasibility, we will evaluate adherence to the study protocol. Patients in the meditation groups will be provided with meditation diaries, where they will be asked to record their daily meditation sessions. Adherence to the meditation schedule will be assessed by calculating the total number of meditation sessions completed divided by the total number of sessions required as per protocol.

### Neurocognitive and psychological assessments

A trained research team member who remains blinded to treatment allocation will perform baseline cognitive, delirium, anxiety, and depression assessments. Cognitive function will be assessed using the Montreal Cognitive Assessment (MoCA), supplemented with days of the week (DOW) and months of the year (MOY) for additional attention testing. The Delirium Symptom Interview (DSI) will be used to capture delirium. The Depression, Anxiety, and Stress scale (DASS-21) will be used to assess the baseline psychological state. Using data from the cognitive testing and DSI, the researcher will complete the Confusion Assessment Method (CAM), which includes an assessment of delirium using the CAM diagnostic algorithm. If this baseline assessment shows a DASS-21 depression score > 10 or MoCA score < 10, the individual will be excluded from the study.

To assess the changes over time, or the possible effect of perioperative meditation, a telephonic MoCA (t-MOCA) will be administered preoperatively within 24 h before surgery. These assessments will take place before initiation of any sedatives or other medications that may affect the patient’s performance or ability to complete the assessment.

On each postoperative day during the hospital stay, a blinded research team member will administer a standard cognitive assessment, including DOW, MOY, CAM, and the DSI. If an individual is intubated postoperatively, a CAM-ICU will be performed instead of a CAM assessment. If daily assessments have plateaued for three consecutive days and the patient remains CAM-negative each day, assessments will then be completed every other day if the individual remains CAM-negative, until the date of discharge. On the day of discharge, the MoCA, DOW, MOY, CAM, DSI, and the DASS-21 will be completed.

A follow-up assessment will be administered at one month (± seven days) after the date of surgery. These will be completed by a blinded research team member via telephone and will include a T-MoCA, DOW, MOY, CAM, DSI, and DASS-21. Medications that were taken 6 h before the assessments, as reported per the individual, will be documented at all time points.

